#### Primary and secondary analyses

The primary efficacy analysis will be conducted on the mITT population, with supportive analyses performed on the PP population. Safety evaluations will utilize the safety set. The primary endpoint analysis will focus on PFS, while secondary endpoints will include response rate, OS, quality of life measures, and safety parameters.

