### Study design

This study is a multicenter, randomized, and controlled clinical study comparing the efficacy and safety of BJOEI combined with BSC versus BSC in patients who are refractory to all available therapy. Eligible patients will be randomized in a 1:1 ratio to either the experimental group or the control group. Both groups will receive BSC in line with the NCCN palliative treatment guidelines (Dans et al., 2021). Participants assigned to the experimental group will be administered 30 mL of intravenous BJOEI daily for 1–14 days in each 28-day cycle. Conversely, the control group will receive only BSC. Treatment for eligible patients will continue until disease progression as defined by the Response Evaluation Criteria in Solid Tumors 1.1 (RECIST 1.1) (Eisenhauer et al., 2009), the onset of unacceptable toxicity, completion of 12 months from randomization, or withdrawal of informed consent. Follow-up evaluations will occur every 2 months until either death, loss of follow-up, or the 12-month mark from randomization. The trial has been registered on the Clinical Trials research platform (ClinicalTrials.gov, ID NCT05897749), and the participant timeline and trial flowchart are displayed in Figures 1, 2, respectively.

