### Outcomes

#### Primary outcome

PFS: PFS is defined as the duration from randomization to the occurrence of tumor progression or death resulting from any cause, whichever transpires first.

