#### Blinding

This is an open-label study where neither participants nor treating physicians are blinded to treatment assignments due to the nature of the interventions. However, to minimize detection and measurement bias, several measures have been implemented for objective assessment of endpoints. Following CONSORT and SPIRIT guidelines, imaging studies for progression-free survival (PFS) will be centrally reviewed by two blinded board-certified radiologists who remain unaware of treatment assignments. Any discordant evaluations will be resolved by a third independent radiologist who is also blinded to treatment allocation. Quality-of-life assessments will be conducted and analyzed by study coordinators and an external data management team, both unaware of treatment assignments. These measures ensure that both objective and subjective endpoints are assessed impartially, minimizing detection and measurement bias despite the open-label nature of the study.

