### Statistical analysis

#### Software and general principles

Data statistical analysis will be conducted using SPSS or SAS software. All analyses will adhere to the intention-to-treat (ITT) principle, encompassing all randomly assigned patients. For participants who withdraw from the trial, their data will be handled using the last observation carried forward (LOCF) method when appropriate.

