#### Analysis populations

We have clearly pre-defined the analysis populations as follows:(1) The modified intention-to-treat (mITT) population will include all randomized patients who receive at least one dose of study treatment (Brucea javanica Oil Emulsion Injection or best supportive care).(2) The per-protocol (PP) population will comprise patients in the mITT population who complete the study without major protocol deviations, specifically defined as patients who receive ≥80% of planned treatment doses, have no prohibited concomitant medications, and complete all required safety and efficacy assessments per protocol schedule.(3) The safety set will include all patients who receive at least one dose of study treatment and have at least one post-baseline safety assessment.

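### The plan sets the primary PFS population in two incompatible ways (ITT on all randomised patients, and a dose-based mITT), and the mITT rule cannot be applied unambiguously when one arm receives only best supportive care

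*Protocol article*

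**What the plan says.** Three parts of the Statistical analysis section of the Protocol article bear on who enters the primary analysis.

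- Software and general principles: "All analyses will adhere to the intention-to-treat (ITT) principle, encompassing all randomly assigned patients".
- Analysis populations: three sets are listed, namely mITT, PP and safety. The mITT set is "all randomized patients who receive at least one dose of study treatment (Brucea javanica Oil Emulsion Injection or best supportive care"). The PP set is a subset of mITT, limited to patients with at least 80% of planned doses, no prohibited medication and complete assessments.
- Primary and secondary analyses: "The primary efficacy analysis will be conducted on the mITT population, with supportive analyses performed on the PP population".

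Three design features matter as well.

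- Primary outcome: "PFS is defined as the duration from randomization to the occurrence of tumor progression or death resulting from any cause, whichever transpires first".
- Blinding: "This is an open-label study where neither participants nor treating physicians are blinded to treatment assignments due to the nature of the interventions".
- Study design: "Both groups will receive BSC in line with the NCCN palliative treatment guidelines". The Intervention section describes BSC as palliative measures and gives it no dose and no first administration. BJOEI is a daily infusion that can be counted.

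**The concern.** If even one randomised patient receives no study treatment, the general principle and the primary-analysis statement cannot both be followed. The supportive analysis does not help, because PP removes more patients than mITT does. The article therefore names no efficacy analysis on all randomised patients, although it says that all analyses are of that kind.

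The mITT rule adds a second problem. Membership depends on something that happens after randomisation, when patient and physician already know the allocation, while the PFS clock has been running since randomisation. Receipt of a first dose can be verified for BJOEI but not for BSC, so the rule leaves room for exclusions that differ between arms. It also leaves room for the reading to be chosen after outcomes are known.

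At stake is the PFS hazard ratio. The article intends it to supply effect-size data for the phase III sample size, and it will also be tested at two-sided 0.05.

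**Working it through.** **Step 1. Is there a figure to reproduce?** No. The sample size is 30 per arm, 2 × 30 = 60, chosen for precision and feasibility. No stated number depends on the analysis set, so the contradiction is established by setting the texts side by side.

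**Step 2. Who is in the primary analysis?**

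| Section | Set | A randomised patient with no study treatment is |
|---|---|---|
| Software and general principles | all randomised, every analysis | included |
| Primary and secondary analyses | mITT (primary) | excluded |
| Primary and secondary analyses | PP (supportive) | excluded |

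**Step 3. What does the mITT rule exclude?** The qualifying treatment is "Brucea javanica Oil Emulsion Injection or best supportive care", and both arms receive BSC.

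- Literal reading: a BJOEI patient who has BSC but no infusion qualifies. Almost nobody is excluded, and mITT is close to ITT.
- Arm-specific reading: study treatment means BJOEI in the experimental arm. A patient who never starts infusions is excluded, while nearly every control qualifies.
- Either reading: a control who withdraws on learning the allocation, before any BSC, could be excluded.

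**Step 4. How large could the bias be?** The article gives no non-starter rate, no prognosis for non-starters and no expected median PFS. The following are assumptions:

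- exponential PFS with a 2-month median and no treatment effect (true hazard ratio 1);
- censoring at 12 months, which matches the planned follow-up;
- would-be non-starters making up 3.3%, 10% or 20% of each arm (on average 1, 3 or 6 of 30);
- non-starter hazard 1, 1.5, 2 or 3 times that of starters;
- complete follow-up of non-starters.

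Cox hazard ratios (BJOEI versus control) from 200,000 simulated patients per arm:

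| Share | Relative hazard of non-starters | ITT | BJOEI non-starters dropped | Controls dropped | Both dropped |
|---|---|---|---|---|---|
| 3.3% | 1.5 / 2 / 3 | 0.998 / 1.004 / 1.001 | 0.987 / 0.988 / 0.979 | 1.010 / 1.022 / 1.024 | 0.999 / 1.005 / 1.002 |
| 10% | 1.5 / 2 / 3 | 1.002 / 1.002 / 0.998 | 0.968 / 0.951 / 0.931 | 1.037 / 1.055 / 1.070 | 1.002 / 1.002 / 0.998 |
| 20% | 1.5 / 2 / 3 | 1.000 / 1.001 / 0.997 | 0.933 / 0.902 / 0.864 | 1.073 / 1.112 / 1.146 | 1.000 / 1.002 / 0.993 |

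With a relative hazard of 1 (average prognosis), every column is 1.00 to within simulation error.

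In 3,000 simulated trials of 30 versus 30 per setting, with only BJOEI non-starters dropped, log-rank rejections favouring BJOEI were 0.035 / 0.040 / 0.051 at 10% (ITT: 0.030 / 0.028 / 0.031). At 20% they were 0.039 / 0.061 / 0.074 (ITT: 0.023 / 0.030 / 0.027).

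**Step 5. Scale.** With a 2-month median and 12 months of follow-up, the expected event proportion is 1 − 2^(−12/2) = 0.984, or about 59 of 60 patients. With 60 events, SE(log HR) ≈ √(4/60) = 0.258, and the 95% CI spans a factor of exp(1.96 × 0.258) ≈ 1.66 each way. A hazard ratio of 0.93 is a shift of |ln 0.93| / 0.258 = 0.073 / 0.258 ≈ 0.28 SE. A hazard ratio of 0.86 is 0.151 / 0.258 ≈ 0.58 SE.

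**The case against.** A reader might infer that only the BJOEI arm can lose patients, so that the hazard ratio is bound to be flattered. The text does not support that. BSC is named as qualifying study treatment and goes to both arms, so a BJOEI non-starter on BSC can stay in mITT, and a control who leaves before any BSC can drop out of it. One-sided exclusion needs the arm-specific reading, which is plausible but not written. Direction and size depend on how many patients do not start, in which arm, and with what prognosis, and the article gives none of these.

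A larger bias is also easy to produce by removing the BJOEI patients whose events came first. With three removed, that gives a hazard ratio of about 0.90–0.91. But it selects on the outcome and allows for no non-starter of ordinary prognosis, so it is close to a worst case.

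Nor is it right to say that the plan has no ITT population at all. The general principle states its membership; the set is merely missing from the list of populations and unused in the primary analysis.

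Finally, this is a pilot, declared not powered for efficacy and hypothesis-generating, and the illustrated shifts lie well inside the confidence interval. That stands, and it limits the harm. It does not settle which set is primary, and a systematic shift in the estimate would still be carried into the phase III calculation.

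**Conclusion.** The contradiction is certain: it is on the page, and nothing else in the article resolves it. It must be settled before outcome data are seen, and the case for a mandatory correction rests on this alone.

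The bias is a conditional risk. Under the arm-specific reading and the assumptions of step 4, the PFS hazard ratio under no effect would be about 0.98–0.99 with 1 of 30 BJOEI patients dropped, 0.93–0.97 with 3 and 0.86–0.93 with 6. If only controls are dropped it moves above 1. It stays at 1.00 if non-starters have average prognosis, if exclusions are alike in both arms, or under ITT with non-starters followed. These shifts are modest beside a confidence interval spanning a factor of about 1.66 each way. The concern is therefore an avoidable distortion of an already imprecise estimate.

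**What to change.** - In Primary and secondary analyses, make ITT the primary set for PFS and OS: all randomised patients, by allocated arm, with time zero at randomisation. Keep mITT and PP as sensitivity analyses.
- In Analysis populations, list the ITT set, and state for each arm what counts as having received study treatment. The PP threshold on planned doses needs the same clarification for BSC.
- Align these two sections with Software and general principles.

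The cost is wording only. Follow-up every 2 months to death, loss to follow-up or 12 months from randomisation is already planned. It should be made plain that patients who never start treatment stay in it, because ITT protects the comparison only if their outcomes are recorded.

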### Statistical significance

All statistical tests will be two-sided, with a significance level of α = 0.05.

## Discussion

CRC stand as a significant global health burden, ranking as the third most prevalent malignancy. Substantial evidence indicates that 90% of CRC cases are diagnosed in individuals aged 50 and above. Alarmingly, the incidence of CRC among younger populations is increasing (Penz et al., 2023). The 5-year survival rate for mCRC remains dishearteningly low at 6% (Coco et al., 2012). The most effective treatment for mCRC is 5-FU-based regimens. However, disease progression after two lines of doublet chemotherapy remains inevitable. Although several drugs are the standard third-line treatment of mCRC in guidelines (Grothey et al., 2013; Dasari et al., 2023; Mayer et al., 2015), they yield minimal response rate and short PFS and OS. In general, the efficacy of third-line and subsequent treatments is unsatisfactory. Few treatment options exist for this population of patients. Traditional Chinese Medicine (TCM) theories and treatment approaches are gaining global acceptance, with integrative Chinese and Western medicine emerging as a novel avenue in cancer therapy. TCM demonstrates unique advantages in tumor treatment. BJOEI have been widely used for the treatment of cancer in China. Numerous clinical studies have shown that BJOEI when combined with FOLFOX/FOLFIRI regimens, enhances tumor treatment efficacy, improves patients' quality of life, and mitigates adverse reactions (Gao and Zhang, 2023).

In prior studies of BJOEI on CRC, the primary endpoint was the ORR. However, this measure alone cannot fully capture the clinical benefits of the trial drug. PFS is utilized both as a surrogate end-point for OS and as a primary trial end-point in itself (Robinson et al., 2014). Therefore, we hope to further objectively evaluate the clinical effectiveness of BJOEI combined with BSC from the PFS status. In addition, Safety assessments will include the incidence, nature, and severity of adverse events; serious adverse events and laboratory abnormalities. Laboratory safety assessments will include the regular monitoring of hematology and blood chemistry.

However, the study design has several limitations. Firstly, obtaining a placebo for BJOEI in China is challenging, making it impossible to blind the study. Secondly, this study is a small-scale trial intended to provide effect size data for calculating sample sizes in future large-scale randomized controlled trials. Thirdly, since the experiment will be conducted in five centers within China, we now clearly state that the findings may primarily reflect outcomes in the Chinese population and that caution should be exercised when extrapolating results to other ethnic groups due to potential pharmacogenomic differences.

The present findings will be hypothesis-generating and will supply the parameters necessary for a rigorously powered confirmatory phase III trial. We anticipate that this trial will offer a new treatment option for advanced CRC patients who are unresponsive to standard therapies.
